## Sample size for qualitative methods:

The sample size for the qualitative component has been determined by the principle of saturation (62); we anticipate that 15 post-intervention interviews will need to be conducted (63). Views of the d-DBT intervention, treatment target preferences, and experiences of assessment schedules will be obtained in individual, semi-structured interviews at intervention completion. Interview data will also be collected on usability of the virtual platform, experiences participating remotely/technical experience, overall perception of the program, and barriers/facilitators to participation. An interview guide will be developed from existing literature, together with feedback from the youth advisory group, and will consist of key questions with prompts to enquire further. All interview data will be transcribed verbatim. Data will be analyzed using the five stages of framework analysis (64). Rigor will be ensured by maintaining an audit trail to foster dependability of the process. Confirmability and credibility will be assured by a team approach to data analysis and discussion of the emerging themes. Consensus of the final theoretical framework, reflexivity, and the impact of the researchers on recruitment, data collection and analysis will also be considered (65).

## Statistical Methods

Data will be analyzed principally using descriptive statistics to assess rates of recruitment, retention, intervention fidelity, engagement, and treatment response. Distributional characteristics of the outcome measures will be assessed for ceiling and floor effects and rates and patterns of missing values. Exploratory trial outcomes including impact of d-DBT on emotional regulation, psychiatric symptoms and functioning will be analyzed using (generalized) linear mixed-effects models with time (baseline, post-treatment), group (d-DBT vs control), time by treatment interaction as the primary predictor. The model will also include covariates to account for pre-treatment clinical characteristics and/or key demographics. The model form will be determined by the distribution features of the outcomes of interest (e.g, continuous, binary or count-type). The efficacy outcome will be impact of d-DBT on functioning, via the Global Functioning: Social and Role Scales. Our prior work with youth has informed us that functioning is more relevant to them than symptom severity (91). Given the small sample size, appropriate to a feasibility trial, we will also calculate point and confidence estimate of effect sizes (Cohen’s *d*) Effect sizes will help with the estimation of the sample size needed for a larger scale confirmatory randomized control trial in the future. Both ITT analysis and per-protocol/completers-only analysis will be conducted to gain insight of estimated efficacy of different subgroups of participants. Full information maximum likelihood approach will be adopted to deal with missing data under the missing-at-random assumption. Diagnostic analysis will be conducted to evaluate the soundness of the statistical assumptions carried by the methods. While the analytic approach can be seen as too complex for the small sample size, it will offer guidance for the analysis plan of the full-scaled trial.

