# CLINICAL TRIAL DESIGN

## Overall Design

This is a multi-methods study employing qualitative and quantitative methods to adapt the d-DBT intervention and test the feasibility, and acceptability of d-DBT in individuals with CHR. d-DBT will first be adapted to CHR individuals in collaboration with a youth advisory group. Then an assessor-masked pilot RCT, where d-DBT will be delivered over 8-weeks, will be conducted. Sixty participants are planned to be enrolled in the RCT, 30 in the d-DBT group and 30 in the treatment as usual group. Participants in the d-DBT group will continue with their standard outpatient care. Outcome measures will be completed at study entry and post-treatment. For the qualitative component of the study, 15 post-intervention semi-structured interviews will be conducted.

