## Quantitative methods

Assessor-masked pilot RCT comparing the adapted d-DBT intervention to standard outpatient care. Participants in the d-DBT arm will receive the intervention over 8-weeks. Measures will be completed at study entry and repeated immediately post-treatment at 8-weeks. Clinician rated assessments will be completed with a trained research assistant who will be unaware of treatment allocation.

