# STATISTICAL PLAN

## Sample Size and Power for quantitative methods

Prior digital intervention feasibility trials in CHR have found that a minimum of 14 participants is sufficient to determine feasibility(90). The sample size was informed by published literature, which suggests 24-70 participants for pilot trials (83-85). We aim to recruit 60 participants in this 8-week pilot RCT to account for potential dropouts (~20%). The proposed sample size will provide reasonably reliable quantitative estimates for the targeted feasibility measures and preliminary data on clinical efficacy. The margins of error for 95% confidence intervals (CI) are ±8.9% for recruitment rate, ±10.1% for adherence/retention/attrition, and ±8.5% for completeness of outcomes. For Aim 3, the minimum detectable effect size is 0.72 (between-group Cohen’s d) and the margin of error for 95% CI is ±0.57 SD.

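### For continuous outcomes, the two-time-point time, group and interaction model leaves the Aim 3 contrast unadjusted for baseline; a common-baseline model estimates the same effect more precisely

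*Protocol*

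**What the plan says.** The Statistical Methods section analyses the exploratory outcomes with (generalized) linear mixed models containing "time (baseline, post-treatment), group (d-DBT vs control), time by treatment interaction as the primary predictor". It continues: "The model will also include covariates to account for pre-treatment clinical characteristics and/or key demographics". The outcome's own baseline value is not named as a covariate, and nothing constrains the arms to a common baseline mean. For missing data, "Full information maximum likelihood approach will be adopted to deal with missing data under the missing-at-random assumption". Both an intention-to-treat and a completers-only analysis are planned.

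The Quantitative methods section fixes two assessments: "Measures will be completed at study entry and repeated immediately post-treatment at 8-weeks". On size, Overall Design says "Sixty participants are planned to be enrolled in the RCT, 30 in the d-DBT group and 30 in the treatment as usual group", and the sample size section allows for about 20% dropout. For Aim 3 it states that "the minimum detectable effect size is 0.72" (between-group Cohen's d) and that "the margin of error for 95% CI is ±0.57 SD".

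**The concern.** With one baseline and one follow-up, a model with a free group main effect treats the baseline difference between arms as something to be estimated, although randomisation makes its expected value zero. The interaction then subtracts the whole observed baseline difference, so chance imbalance enters the estimate at full weight instead of being weighted by how well baseline predicts week 8.

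The covariate sentence looks as though it supplies the missing adjustment. Entered as a main effect, a pre-treatment covariate shifts both time points equally and does not adjust the interaction for baseline.

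At stake is the precision of the Aim 3 effect estimates. The protocol intends these to help size a confirmatory trial, and it intends the analysis approach to guide that trial's plan.

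**Working it through.** **Inputs.** From the protocol: 30 randomised per arm, about 20% dropout (so 24 followed up per arm), and two time points. Assumed, because the protocol does not state them: two-sided 5% level, 80% power, and rho from 0.3 to 0.9. Sigma is the outcome SD, taken as equal at both times.

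**The protocol's own figures.**
- Margin of error: 1.96 × sqrt(2/24) = 0.566, which matches ±0.57. With 30 per arm it would be 0.506.
- Detectable effect: (1.96 + 0.84) × sqrt(2/30) = 0.723, which matches 0.72. With 24 per arm it would be 0.81.

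Both are plain two-group comparisons that use no correlation, and they rest on different sample sizes (24 and 30 per arm).

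**Is the interaction a change score?** In one simulated complete data set (30 per arm, rho 0.5), a random-intercept mixed model with time, group and interaction gave 0.3509. The raw difference in mean change was also 0.3509. Adding an unrelated-to-treatment covariate as a main effect left it at 0.3509, and so did adding the baseline score itself. Removing the group main effect gave 0.3696, an estimate adjusted for the baseline difference.

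**Variance, completers (n per arm).**
- Planned: 2(1 − rho) × 2 sigma²/n.
- Common baseline: (1 − rho²) × 2 sigma²/n.
- Ratio: (1 + rho)/2, so the reduction is (1 − rho)/2.

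**Variance under FIML (30 baselines, 24 follow-ups per arm).**
- Planned: 2 sigma² × [(1 − rho²)/24 + (1 − rho)²/30].
- Common baseline: about 2 sigma² × (1 − rho²)/24.

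At rho 0.5, the planned variance is 2 × (0.75/24 + 0.25/30) = 0.0792, giving a half-width of 1.96 × sqrt(0.0792) = 0.551. The common-baseline variance is 2 × 0.75/24 = 0.0625, giving 0.490. The reduction is 1 − 0.0625/0.0792 = 21%.

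| rho | Reduction, completers | Reduction, FIML (simulated) | 95% half-width in SD under FIML, planned vs common baseline | Detectable effect under FIML, planned vs common baseline |
|---|---|---|---|---|
| 0.3 | 35% | 30% (28%) | 0.646 vs 0.540 | 0.92 vs 0.77 |
| 0.5 | 25% | 21% (18%) | 0.551 vs 0.490 | 0.79 vs 0.70 |
| 0.6 | 20% | 17% (not run) | 0.496 vs 0.453 | 0.71 vs 0.65 |
| 0.7 | 15% | 12% (11%) | 0.432 vs 0.404 | 0.62 vs 0.58 |
| 0.8 | 10% | 8% (6%) | 0.354 vs 0.339 | 0.506 vs 0.485 |
| 0.9 | 5% | 4% (2.5%) | 0.252 vs 0.247 | 0.360 vs 0.353 |

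The simulated figures come from 20,000 trials per row with 6 of 30 per arm lost at random. They include the small cost of estimating the baseline slope. Both estimators were unbiased: the true effect was 0.30 and the means across all runs were 0.296 to 0.302.

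**Against the stated margin.** The planned FIML variance equals the unadjusted 2/24 when (1 − rho²) + 0.8(1 − rho)² = 1, that is rho² + 8 rho − 4 = 0, so rho = 0.47. Below that the planned interval is wider than the stated one. For completers the crossing is where 2(1 − rho) = 1, at rho 0.5, and the half-width is 0.62 at rho 0.4 and 0.67 at rho 0.3. The common-baseline half-width, 1.96 × sqrt(2(1 − rho²)/24), cannot exceed 0.566 in large-sample terms.

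**The case against.** The planned model is standard, valid and unbiased under randomisation. The primary outcomes are feasibility, acceptability and usability; Aim 3 is called exploratory and no primary outcome rests on this interaction. On this view, preferring a constrained model is a matter of taste, and the handling of covariates could be settled in a statistical analysis plan. The part about validity and consequence stands, and it caps the weight of the point. But the protocol itself fixes the model terms, including the free group effect, so the inefficiency is written in. On covariates, the protocol does not say whether they enter as main effects only, so that part of the point is conditional on their doing so.

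A reader might infer that the gain is a firm 15% to 35% for every outcome and free of conditions. The documents do not support that:
- The range needs rho between 0.3 and 0.7, which the protocol does not give, and complete data, which it does not expect. Under the planned dropout and FIML the gain is smaller, and it nearly vanishes at high rho.
- The change-score identity is exact only for linear models with complete data. It does not carry over exactly to the binary and count models the protocol also allows.
- A common baseline mean requires baseline scores unaffected by allocation. Research Visits places baseline after screening, but no section says when randomisation occurs relative to it.

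A reader might also infer that the stated ±0.57 SD is unattainable under the planned model. It is not: at rho 0.5 the planned FIML half-width is 0.551, and at rho 0.7 it is 0.432. At rho 0.7 the change of model brings it only to 0.404, a small difference for a pilot.

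**Conclusion.** The point holds as an efficiency improvement for continuous outcomes. It is not an error in the plan, and it introduces no bias to correct. Under the planned FIML analysis the variance saving is about 30%, 21% and 12% at rho 0.3, 0.5 and 0.7, and under 10% from about 0.8. In the planned completers analysis it is 35%, 25% and 15% at the same three values.

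The gain matters most if rho is low. Below about 0.47 (FIML) or 0.5 (completers), the planned contrast is less precise than a simple comparison of week-8 means, which is the basis of the stated margin. All sizes depend on an assumed rho, equal variances at the two times and, for FIML, 24 of 30 followed up per arm. The case for acting is that the change is cheap and that these estimates and this model are meant to inform the larger trial.

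**What to change.** For continuous outcomes only, replace the model sentence with one that omits the group main effect: fixed effects for time and time-by-group, so that the randomised arms share one baseline mean, with an unstructured 2×2 covariance for the two assessments. State that other pre-treatment covariates enter with a time interaction. Participants with a baseline but no week-8 value stay in the likelihood, as the protocol intends.

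For the completers-only analysis, a week-8 ANCOVA on the baseline score gives essentially the same estimate. It should not simply be substituted in the intention-to-treat analysis, because ordinary ANCOVA drops participants with baseline only.

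Confirm in the protocol that baseline assessment precedes allocation, or is unaffected by it. This matters particularly for the self-reported scales.

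The cost is a sentence or two of analysis wording and a clarification of timing. No extra data are needed, and the model has one parameter fewer before any covariate-by-time terms are added.

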# SAFETY AND ADVERSE EVENTS

Adverse Events (AEs) and Serious Adverse Events (SAEs) will be documented and reported as mandated by current regulations. AEs will be assessed at each study visit. Any AEs will be followed up to resolution or appropriate resolution will be taken as per the direction of the QI. All AEs, whether reported by the participant or observed by study staff/investigators, will be recorded on the AE log along with a brief description, start date/resolution date and any action taken. The AE log will be initialed by the QI, who will make the determination on the seriousness, relationship, and expectedness of the AE to the investigational drug/study procedures. Where the event is deemed to meet CAMH REB reporting criteria, the QI will notify REB in accordance with CAMH REB’s reporting requirements and timelines.

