## Risks/Benefits

There are no anticipated risks to the participants as the intervention is a ‘light-touch’ psychosocial intervention. It is incumbent upon the research team to identify subjects who require treatment and actively assist them in getting it. Anyone identified with acute psychosis or at acute risk of suicide will be assisted to immediately contact local mental health professionals. If required, the research team will accompany the participant to the local mental health service provider. We have developed a standard operating procedure for risk management that will be adhered to throughout the study. All assessments will be completed in accessible, private, and appropriate venues that suit the needs and preferences of participants. The appointments will be scheduled at times convenient to participants, considering education, household commitments and employment commitments. Participants will not be exposed to a risk of physical and mental harm that is greater than that typically encountered in normal life and the recruitment materials will direct participants to relevant supports if participation raises any concerns. The Digital Navigator will connect with participants weekly, if there are any concerns about risk they will follow our risk management protocol.

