**Fidelity**

d-DBT will be delivered virtually in a self-led program. This eliminates the concern of inter-practitioner variability in delivering psychotherapy. There will be weekly check-ins with our research staff who will act as ‘digital navigators’ and provide non-clinical support around application use which may include application troubleshooting, guidance through application exercises, reminders, and encouragement to support engagement (81). They will have a semi-structured script which will explore if participants have been able to complete modules, explore barriers, and help answer basic questions about the content of the modules. We will also use the DBT ways of coping checklist to measure DBT-skills use (82).

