**Control Group Procedures**

Participants in the control group will continue to receive treatment as usual, which may consist of routine appointments with healthcare providers, medication management, and other supportive services as deemed necessary by their care team. Outcome measures will be collected at study entry and at 8-weeks for participants in the treatment as usual group.

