## Participant Compliance Monitoring

Poor engagement and attrition from digital interventions is an increasingly recognized challenge for interpreting and translating the findings from digital health research. Meta-analysis has reported that 26% of individuals dropout of digital interventions for depressive symptoms (39), whereas premature termination of in person psychotherapy is estimated at 20% (40). The addition of a human component reduces attrition by more than 50% (39), therefore this study intends to use digital navigators to troubleshoot technical issues and enhance therapeutic alliance (34). Digital navigators will complete brief virtual check-ins with participants every week during the intervention. This will help enhance retention and engagement and identify any potential barriers participants are having to complete their module.

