## Schedule of Events

| **Procedures** | Screening | Baseline | d-DBT Intervention (8 weeks) | Follow up Visit |
| --- | --- | --- | --- | --- |
| Informed consent | X |  |  |  |
| Inclusion/Exclusion Determination | X |  |  |  |
| SCID for the DSM-5 | X |  |  |  |
| SIPS | X |  |  | X |
| Prevention through Risk Identification, Management and Education Screen-Revised |  | X |  | X |
| Connor-Davidson Resilience Scale |  | X |  | X |
| Brief Difficulties in Emotion Regulation Scale (DERS-16) |  | X |  | X |
| Borderline personality dimensions: BSL-23 |  | X |  | X |
| Calgary Depression Scale for Schizophrenia |  | X |  | X |
| The State-Trait Anxiety Inventory |  | X |  | X |
| Global Functioning: Social and Role Scales |  | X |  | X |
| Timeline Follow Back (TLFB) |  | X |  | X |
| Adolescent Alcohol and Drug Involvement Scale (AADIS) |  | X |  | X |
| The Cannabis Use Disorders Identification Test-Revised (CUDIT-R) |  | X |  | X |
| The Daily Sessions, Frequency, Age of Onset and Quantity of Cannabis Use Inventory (DFAQ-CU) |  | X |  | X |
| Columbia-Suicide Severity Rating Scale |  | X |  | X |
| MATRICS Consensus Cognitive Battery (MCCB) |  | X |  | X |
| d-DBT program |  |  | X |  |
| DBT ways of coping checklist to measure DBT-skills use |  |  |  | X |
| Complete Case Report Forms (CRFs) | X | X | X | X |
| Client Satisfaction Questionnaire |  |  |  | X |
| System Usability Scale (SUS) |  |  |  | X |
| Adverse Event Log | X | X | X | X |
| Qualitative Interview |  |  |  | X |

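### By-arm adverse event summaries would rest on unequal ascertainment: weekly staff contact under d-DBT, no scheduled research contact between baseline and week 8 under treatment as usual

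*Protocol*

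**What the plan says.** Safety and Adverse Events gives the general rule, "AEs will be assessed at each study visit", and then a broad recording rule: "All AEs, whether reported by the participant or observed by study staff/investigators, will be recorded on the AE log". The log contents named there are a short description, start and resolution dates and any action taken, with the qualified investigator's judgement of seriousness, relationship and expectedness. How or from whom the event was learned is not among them.

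The Schedule of Events marks the log in all four columns ("Adverse Event Log | X | X | X | X"). The only column between baseline and follow-up is headed "d-DBT Intervention (8 weeks".

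Contact during those weeks differs by arm:

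- **d-DBT.** Participant Compliance Monitoring states: "Digital navigators will complete brief virtual check-ins with participants every week during the intervention". Risks/Benefits gives this contact a safety role: "The Digital Navigator will connect with participants weekly, if there are any concerns about risk they will follow our risk management protocol". Fidelity describes its content as technical and motivational; staff "provide non-clinical support around application use", and no adverse event question is mentioned.
- **Treatment as usual.** Control Group Procedures states: "Outcome measures will be collected at study entry and at 8-weeks for participants in the treatment as usual group". Routine clinical care continues, but no research contact is scheduled in between.

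**The concern.** How many adverse events a trial records depends on how often someone is in a position to hear of them. Here that opportunity differs by randomised arm, and the recording rule turns whatever is heard into a log entry. A by-arm count would then mix any effect of d-DBT with the effect of being telephoned weekly. Two wrong readings become possible: a harmless programme looks harmful, or a genuine excess is dismissed as extra contact.

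Clinical Data to Date says that d-DBT has not been used in this population before, and Statistical Methods says that the pilot is meant to guide a full-scale trial. Its adverse event counts are therefore likely to be read as early safety evidence even without a formal test.

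A later analysis plan can choose how to tabulate events. It cannot separate check-in disclosures from visit reports if the source was never recorded, nor supply a common question that was never asked. That makes this a data-collection matter for the protocol.

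**Working it through.** The protocol gives no adverse event rate, detection probability or safety figure, so there is no stated number to reproduce. The check is a count of contacts, a reading of the logging rule, and an illustration under assumed inputs.

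**1. Scheduled research-staff contacts after baseline**

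| Arm | Weekly check-ins | Week-8 visit | Total |
| --- | --- | --- | --- |
| d-DBT | 8 | 1 | 9 (8 if the last check-in coincides with the visit) |
| Treatment as usual | 0 | 1 | 1 |

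**2. Does a check-in disclosure reach the log?** Navigators are research staff (Fidelity). The recording rule covers anything a participant reports or staff observe, and the log is marked for the intervention period. An event mentioned at a check-in must therefore be logged. Because no adverse event question is specified for the check-in, this capture is opportunistic, not systematic.

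**3. Direction.** With equal true risk, extra opportunities in one arm can only add recorded events in that arm. The expected bias is towards more events under d-DBT.

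**4. Illustrative size (all inputs assumed except 30 per arm, from Overall Design)**

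*Relative capture.* Let both arms have true risk p = 0.40, let weekly contact capture everything, and let one 8-week recall capture a fraction c of that. The apparent risk ratio is p / (p × c) = 1/c.

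- d-DBT: 0.40 × 30 = 12 participants with a recorded event.
- Control, c = 0.5: 12 × 0.5 = 6 of 30 (20%); ratio 2.0; excess 20 points.
- Control, c = 0.8: 12 × 0.8 = 9.6 of 30 (32%); ratio 1.25; excess 8 points.

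*Recall decay.* Let events fall uniformly over the 8 weeks and recall decay with half-life h weeks, k = ln 2 / h. The mean proportion recalled over a window of T weeks is (1 − exp(−kT)) / (kT).

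| h (weeks) | T = 1 | T = 8 | Ratio |
| --- | --- | --- | --- |
| 2 | 0.845 | 0.338 | 2.50 |
| 4 | 0.918 | 0.541 | 1.70 |
| 8 | 0.958 | 0.721 | 1.33 |
| 16 | 0.979 | 0.845 | 1.16 |

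Both calculations treat each weekly contact as a proper enquiry, which the protocol does not say it is. If the check-ins elicited nothing beyond the week-8 enquiry, the ratio would be 1.00.

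**5. Against chance variation.** The 95% half-width for 40% versus 32% is 1.96 × √(0.40 × 0.60/30 + 0.32 × 0.68/30) = 1.96 × 0.1235 = 0.24. An 8-point artefact would lie well inside the noise of a single trial of this size, although it would still shift the expected counts.

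**6. After the fix.** With the same enquiry in both arms, c = 1 apart from residual recall differences, and the expected ratio under equal risk is 1.00.

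**The case against.** The strongest reply is that no safety comparison exists to be biased. The aims, the outcome lists and Statistical Methods contain no adverse event endpoint or safety test, and the safety section is about handling individual events. The scheduled enquiry is arguably equal too: Research Visits describes entry and week-8 assessments for everyone, check-ins are not called visits, and the mark in the intervention column may only mean that the log stays open. Much of this stands. It limits the point to descriptive by-arm summaries and makes check-in capture opportunistic. It does not remove the asymmetry, because an event disclosed at a check-in must be logged whether or not anyone asked for it.

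A reader might also infer more than the documents support:

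- *That control-arm events rest on a single recall.* Controls continue routine appointments, chart information may be used for research purposes (Participant Recruitment and Screening), and spontaneous reports are logged in either arm.
- *That measurement of suicidality or psychosis symptoms is biased.* The C-SSRS and SIPS are scheduled before treatment and at follow-up without distinction by arm.
- *That the investigator's benefit-to-risk review in Data Management is distorted between arms.* That sentence concerns the clinical and cognitive assessments, which both arms undergo.
- *That a risk ratio of 1.25 to 2.0 is an estimate.* It is arithmetic on assumed inputs.

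Finally, it is fair to say that the remedy is incomplete: participants who talked an event over with a navigator may remember it better at week 8.

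**Conclusion.** The point holds for any by-arm description of adverse events. Followed as written, the protocol gives d-DBT participants about 8 additional occasions on which an event may be disclosed and must then be recorded, with no scheduled counterpart for controls. The expected direction is more recorded events under d-DBT regardless of true harm. The size is not derivable from the document; the assumed inputs above give ratios between 1.16 and 2.50, and less if check-ins rarely prompt disclosure.

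This does not touch the feasibility and acceptability aims and invalidates no planned test. It should still be settled before enrolment, because the log as described does not record source and the two kinds of report would be hard to separate afterwards.

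**What to change.** Amend Schedule of Events and Safety and Adverse Events as follows:

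1. At the week-8 visit, ask participants in both arms the same fixed adverse event question, covering the whole period since baseline.
2. Add a field to the adverse event log for the source of each report: visit, check-in, chart or spontaneous.
3. State that any between-arm summary of adverse or serious adverse events uses only sources common to both arms: the week-8 question, the week-8 C-SSRS and, if charts are used, the same look-up over the same period in both arms. List events learned only at navigator check-ins separately, as surveillance available in the d-DBT arm alone. They continue to be logged and handled for safety as now.

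The cost is protocol wording, one question at an existing visit, one log field and, if charts are used, a short look-up. No control-arm contacts are added, so treatment as usual is unchanged. The downsides are that the comparative table omits d-DBT events mentioned only at check-ins, and that some differential recall at week 8 may remain.
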